## Abstract

**Background:**

Despite limited effectiveness of short-term psychotherapy for chronic depression, there is a lack of trials of long-term psychotherapy. Our study is the first to determine the effectiveness of controlled long-term psychodynamic and cognitive-behavioral (CBT) treatments and to assess the effects of preferential vs. randomized assessment.

**Methods/design:**

Patients are assigned to treatment according to their preference or randomized (if they have no clear preference). Up to 80 sessions of psychodynamic or psychoanalytically oriented treatments (PAT) or up to 60 sessions of CBT are offered during the first year in the study. After the first year, PAT can be continued according to the ‘naturalistic’ usual method of treating such patients within the system of German health care (normally from 240 up to 300 sessions over two to three years). CBT therapists may extend their treatment up to 80 sessions, but focus mainly maintenance and relapse prevention. We plan to recruit a total of 240 patients (60 per arm). A total of 11 assessments are conducted throughout treatment and up to three years after initiation of treatment. The primary outcome measures are the Quick Inventory of Depressive Symptoms (QIDS, independent clinician rating) and the Beck Depression Inventory (BDI) after the first year.

**Discussion:**

We combine a naturalistic approach with randomized controlled trials(RCTs)to investigate how effectively chronic depression can be treated on an outpatient basis by the two forms of treatment reimbursed in the German healthcare system and we will determine the effects of treatment preference vs. randomization.

**Trial registration:**

http://www.controlled-trials.com/ISRCTN91956346

## Background

Based on a recent review, each year 38.2% of the EU population suffers from a mental disorder. Depression has been identified as the most disabling disease affecting about 17% of the population during their lifetime [1]. According to the WHO, depression will be the second most frequent illness and will carry the highest load of impairment of quality of life worldwide in 2020. Parental chronic depression is also a heavy burden for children [2]. Only 50% of all depressed patients recover within six months and two-thirds within one year, while 6% to 7% are still depressed after 10 to 15 years. There is a high danger of a chronic course of depression, as 30% of all episodes of depression last longer than two years. Half of the patients relapse after their first episode, 70% after the second, and 90% after their third episode [3]. While medication has evolved as the most frequent first-line approach to the treatment of depression, 20% to 30% of patients have not responded to medication; one-third of those responding relapse within one year, and 75% relapse within five years.

In more than 80 randomized controlled trials (RCTs), cognitive behavioral therapy (CBT) has been established as an effective treatment for depression [4-6]. In a recent meta-analysis [7] based on 23 studies totaling 1,365 subjects, this could also be established for short-term psychodynamic psychotherapy (STPP). Compared with other psychotherapies (usually CBT), a small but significant effect size (*d* = −0.30) was found, indicating the superiority of other psychotherapies immediately post-treatment, but no significant differences were found at 3-month (*d* = −0.05) and 12-month (*d* = −0.29) follow-ups.

So far, the evidence for psychotherapy of depression rests on short-term treatments [6-8]. Unlike the results for the treatment of acute depression, psychotherapy, findings of the effects for chronic depression (dysthymia or major depressive episodes) have been limited [8]. In addition, short-term treatments offered in randomized controlled trials lack external validity. Unlike the treatments performed in clinical trials, psychotherapies in clinical practice throughout Europe are of considerably longer duration (CBT up to 60 sessions, psychodynamic treatment up to 80, psychoanalysis up to 240 to 300 sessions). Positive long-term effects of psychoanalysis and psychoanalytic long-term treatments were shown in a representative, multi-perspective and retrospective study [9]. Yet, up until now, there are no controlled studies available comparing psychoanalysis (PAT) and cognitive behavior therapy (CBT) directly [10,11]. However, a few clinical reports [12] comparing psychoanalytic and cognitive-behavioral long-term therapy exist. They demonstrate that even when psychoanalysts and behavior therapists treat similar disorders with similar success rates, the patients differ in many ways.

### Patient preferences

Patient preferences have been identified as one of the three key components of evidence-based medicine, along with the best available research and clinical expertise. They can be defined as the behaviors or attributes of the therapist or therapy that patients value or desire. Regardless of the therapeutic model, engaging patients to become active in psychotherapy is a crucial variable [13]. Patient preferences are particularly important in psychoanalytic long-term therapies with chronically, severely ill patients who have already undergone several unsuccessful therapies [9].

Role preferences involve the behaviors and activities that clients desire themselves and their therapists to engage in while in therapy (for example, preferring the therapist to take an active advice-giving or a listening role, preferring a group or an individual format). Therapist preferences entail characteristics that clients hope their therapists will possess (for example, extended clinical experience, similar ethnic background). Treatment preferences include specific desires for the type of intervention that will be used (for example, a behavioral or a psychodynamic approach, psychotherapy or pharmacotherapy).

A recent meta-analysis [14] of 35 studies found that patients who were matched to their preferred treatment were less likely to drop out (OR = 0.59; *P* < 0.001) and showed greater improvement (*d* = 0.31; *P* < 0.001). Type of preference (role, therapist, treatment) had no specific effect, but type of design was a significant moderator with greatest effects in RCTs. Assignment by chance may or may not meet a patient’s preference. Patients with strong preferences may refuse randomization and therefore threaten the external validity of an RCT.

Therefore, we decided to use a complex controlled design with a patient’s preference arm (assignment of patients according to their treatment preference) and a randomization arm (assignment of patients by chance). Thus, we are able to include patients who refuse randomization. However, to articulate preferences, patients need to know the alternatives. Even patients who have already undergone psychotherapy are often unable to specify what specific form of treatment they had, for example, both PAT and CBT are described as some kind of talking cure. To capture patients’ preferences, we provided all patients with brief descriptions of both treatments offered in this trial before their decisions for preference of randomization.

## Methods

### Study centers

The study is carried out at the following clinical sites: the Sigmund Freud Institute at Frankfurt, the Department of Psychology at the Frankfurt University, the Department of Psychosomatic Medicine and Psychotherapy at University Medicine Mainz, the Department of Psychology at the University of Mainz, the Department of Psychosomatic Medicine and Psychotherapy at the University Clinic Hamburg-Eppendorf, the Department of Psychosomatic Medicine at University Clinic Benjamin Franklin and clinics in the Theodor-Wenzel-Werk Berlin, and the Department of Psychology at the Free University Berlin. These sites are responsible for screening, information, and independent assessment of all patients treated by licensed psychotherapists (PAT or CBT), either in an outpatient unit or in private practice. We have taken care to include different areas of Germany (middle, and north) and institutions, in order to include a broad range of patients and therapists. The Department of Psychology at the University of Tübingen is responsible for CBT training and supervision at all clinical sites. The center for documentation, statistics, and data analyses at the Ludwig-Maximilians University Munich is an independent site that performs data monitoring, randomization, and statistical evaluation. Patients were recruited through outpatient clinics and private practice. In all cases, assessments are conducted by independent, trained, and supervised clinicians, who are blind to the intervention.

### Participants

We include patients between 21 and 60 years of age suffering from chronic depression. Patients have to be depressed for more than one year and currently meet a diagnosis of major depression or dysthymia. In addition, their current depression has to be of a certain severity, meeting a Beck Depression Inventory (BDI - self-report) score above 17 and aclinician-rated Quick Inventory of Depressive Symptoms (QIDS-C) score of more than 10 points. These inclusion criteria and the exclusion criteria are listed in Table 1. Patients can be on antidepressant medication but still meet the inclusion criteria. Patients on medication have to be on a stable dosage for more than four weeks. After information and discussion of the study protocol, the required assessments over three years, and the study interventions, patients have to sign an informed consent sheet before starting baseline assessment and either preferred or randomized treatment.

**Table 1 T1:** Inclusion and exclusion criteria

Inclusion criteria	▪Diagnosis of major depression or dysthymia (based on Structured Clinical Interview - SCID) for at least 12 months
	▪QIDS-C score > 10; BDI 2 >17
	▪Complaints for at least 12 month
	▪Age: 21 to 60 years
	▪Sufficient knowledge of the German language
	▪Informed consent with the study protocol
Exclusion criteria	▪Current or past psychotic symptomatology, schizoaffective, schizophrenic, or bipolar affective disorder
	▪Substance dependence current or during the last three years
	▪Dementia
	▪Borderline, schizotypal and antisocial personality disorder
	▪Acute suicidality
	▪Restriction of intellectual capacity
	▪Serious physical illness that strongly affects the depression or is causal for the depression
	▪Concurrent psychotherapeutic treatment

### Intervention: psychoanalytic therapy

Psychoanalytic psychotherapeutic and psychoanalytic strategies are well developed for severely and chronically depressed patients with comorbid conditions [15-18]. Psychoanalytic authors always consider depression in the context of developmental processes, particularly pathological processes determined by unconscious fantasies and conflicts (a) concerning a differentiated, integrated, and realistic basic feeling of self and identity; (b) concerning the ability to engage in satisfying reciprocal interpersonal relationships; and (c) concerning the ability to unfold one’s own creativity in work, developmental tasks matching the patient’s lifecycle, and satisfying management of everyday life situations. Discovering the unconscious determining factors due to failures in the development (archaic unconscious fantasies stimulated by traumatizations, pathological relationships, burdened life situations, etc.) and working through idiosyncratic unconscious fantasies and conflicts due to developmental deficits and traumatizations in the ‘here and now’ of the therapeutic relationship is seen as indispensable for a long-lasting change of depressive symptoms. Thus, different forms of depression are not understood as clearly distinct entities due to specific genetic or neurobiological factors, but as products of complex interactions between genetic vulnerabilities and experiences in early relationships leading to pathological fantasies, developments, and adaptations. They constitute maladaptive attempts of the individual to cope with severe and lasting disruptions of his normal development.

All psychoanalytic study therapists were trained in the Tavistock manual for treating chronic depressed patients [18] in a workshop. This manual details psychoanalytic techniques to be applied with this group of patients, illustrated by clinical ‘anchor examples’. Pretested in a British trial with chronically depressed patients, it specifies a therapeutic approach, including establishing emotional contact, receptivity and openness, identification of fears, activity, and work in the ‘here and now’ and in transference. A psychodynamic model of the evolvement of chronic depression provides a background of specific interventions. Participating psychoanalysts have had at least three years of clinical practice, participate in regular supervision groups, and record at least 30 therapy sessions, to permit independent control for adherence and competence.

### Intervention: cognitive behavior therapy

Cognitive and behavior therapy for depression was developed by Beck, Rush, Shaw, and Emery [19] and Lewinsohn, Munoz, Youngren, and Zeiss [20]. Their manuals are adapted and integrated in a widely used and well-accepted CBT for depression [21]. Nearly all licensed behavior therapists are familiar with this manual and material, and have received formal training in using the manual. In general, CBT with depressed patients follows five phases within 25 to 45 sessions:

· Phase 1: Development, biographical information, problem analysis, goals, psychoeducation, rationale for treatment, explanation of intervention steps.

· Phase 2: Behavior oriented interventions, activation, increasing pleasant activities, balance of negative and positive activities, situation analysis, structuring day and week.

· Phase 3: Cognitive interventions, thought control, focus on automatic thoughts and alternatives, influence basic assumptions and schemata.

· Phase 4: Skill training, social skills, problem-solving skills, communication skills, role play, stress management, etc.

· Phase 5: Maintenance, prepare for crisis and beginning depression, relapse prevention, transfer into everyday life.

This basic CBT for depression can be extended for chronic depressed patients by intervention elements and strategies (for example, situational analysis, skill training, disciplined self-disclosure) of cognitive behavioral system of psychotherapy [22]. All the study CBT-therapists are well trained and state licensed. They see patients regularly, either in their own private practice or as therapists in cooperating outpatient units. Furthermore, they all participated in an initiating workshop about CBT of chronic depression and were supervised throughout the study. Supervision was offered at each site by experienced senior behavior therapists. In addition, at each site, additional workshops about CBASP or MBCT, or both, were held for the study therapists. Each therapy session is taped and a selection of tapes of each therapy will be rated to control for adherence to cognitive behavior therapy and for therapists’ competence.

### Assessments

The time points of assessment and the measures are presented in Table 2. Assessment is conducted before assignment to treatments, and over a course of three years. Patients are assessed (structured clinical interview, SCID; quick inventory of depressive symptoms, QIDS) by independent and trained clinicians, who are blind to treatment conditions. We took great care to characterize patients by psychoanalytically oriented characteristics of psychic structure and conflict [23-25].

**Table 2 T2:** Planned assessments in the course of the trial (t7 to t10 are options for extension, depending on funding)

**Measure point**	**Patient**	**Therapist**	**Diagnostician**
**t0 intake**	BDI-2, SCL90-R, DAS, DEQ, CTQ, IIP		SKID I/II, QIDS-C, OPD-2, HUS, SRS, SOFAS
t1 (weekly, weeks 1–6)	QIDS-S, HAQ	QIDS-C, HAQ	
t2 (3 mo)	QIDS-S, HAQ	QIDS-C, HAQ	
t3 (6 mo)	QIDS-S, HAQ	QIDS-C, HAQ	
**t4 main assessment (12 mo)**	BDI-2, SCL-90R, DAS, DEQ, IIP, HAQ	QIDS-C, HAQ	LIFE, QIDS-C, OPD-2, HUS, SRS, SOFAS
t5 (18 mo)	QIDS-S, HAQ	QIDS-C, HAQ	
**t6 main assessment (24 mo)**	BDI-2, SCL-90R, DAS, DEQ, IIP, HAQ		LIFE, QIDS-C, HUS, SRS, SOFAS
t7 (30 mo)	QIDS-S, HAQ	QIDS-C, HAQ	
**t8 main assessment (36 mo)**	BDI-2, SCL-90R, DAS, DEQ, IIP, HAQ	QIDS-C, HAQ	LIFE, QIDS-C, OPD-2, HUS, SRS, SOFAS
**t9 main assessment (48 mo)**	BDI-2, SCL-90R, DAS, DEQ, IIP, HAQ		LIFE, QIDS-C, HUS, SRS, SOFAS
**t10 final assessment (60 mo)**	BDI-2, SCL-90R, DAS, DEQ, IIP, HAQ		LIFE, QIDS-C, OPD-2, HUS, SRS, SOFAS

Notes: *BDI 2* Beck Depression Inventory II, *CTQ* Childhood Trauma Questionnaire, *DAS* Dysfunctional Attitude Scale, *DEQ* Depressive Experience Questionnaire, *HAQ* Helping Alliance Questionnaire (patient-, therapist-form), *HUS* Heidelberger Restructuring Scale, *IIP* Inventory of Interpersonal Problems, *LIFE* Longitudinal Follow-up Evaluation, *OPD-2* Operationalized Psychodynamic Diagnostics, *PEI* Psychoanalytic Intake Interview, *QIDS* Quick Inventory of Depressive Symptoms [self- (QIDS-S) and clinician-rating (QIDS-C)], *SCID I, II* Structured Clinical Interview according to DSM-IV, *SCL-90R* Symptom-Checklist, *SOFAS* Social functioning, *SRS* Self-Reflective Functioning Scale.

### Objectives and hypotheses

The purpose of the trial is to address the following issues:

▪ Short- and long-term efficacy of the two treatments (PAT, CBT).

▪ Course and stability of treatment effects.

▪ Impact of randomization compared with preference for both treatments.

▪ Health costs (work loss, hospitalization, outpatient treatment, drugs, etc.).

### Hypotheses

A. Effectiveness and comparison of the two treatments with the chronically depressed: Both psychotherapies lead to positive effects concerning (a) the reduction of depressive symptoms (QIDS, BDI), (b) the proportion of remitted patients (LIFE), (c) improved social functioning (SOFAS), (d) a decrease of continuous antidepressant medication. These effects are manifested at the main assessments (see Table 2: t4, t6, t8) a cross the trial. The courses of change differ between PAT and CBT: (a) CBT achieves faster symptom reduction, (b) PAT starts slowly but achieves more stable, lasting effects (this is evidenced in the process measures, the rates of response and the symptom level at follow-up (see Table 2: t6, t8, t10).

B. Comparison of preferred and randomized therapies: Preferred therapies are expected to lead to stronger effects and less study drop-outs than randomized therapies. Patient preference is particularly important in PAT. Therefore, we expect larger effect differences between PAT preference and PAT randomization compared with CBT.

C. Health costs and cost effectiveness. We expect a significant reduction of the days of absence from work and of further treatment needed (for example, hospitalization) for both therapies. We expect larger health-cost reductions for PAT compared with CBT in the long term. We expect that treatment costs for CBT will be lower than those for PAT, resulting in a better cost-benefit ratio.

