### Design

The trial will include about 360 chronically depressed outpatients. About 180 patients will have a clear preference foreither PAT or CBT. After baseline assessment (t0) they will be assigned to a study therapist offering the preferred intervention. About 180 patients will come without preference and accept to be randomized to either PAT or CBT. Randomization will take place after baseline assessment (t0). Figure1 summarizes the 2 (preference) by 2 (psychotherapies) by 4 (time) factorial design.

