### Secondary analyses

Self-report questionnaires and observer ratings will be analyzed by mixed models with repeated measurements. With two co-primary outcomes, we will conduct the tests at a 0.025 level of significance (two-tailed) to adjust for the multiple comparison issue. Further analyses will include cross-sectional analyses to compare therapists; subgroup analyses of subjects’ and therapists’ conditions; and costs of the SP treatment.

Descriptive statistics showing the measurements over time will be presented whenever appropriate. Serious adverse events and cases of drop-outs will be analyzed descriptively.

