### Randomization

As Figure1 shows, in a partial randomization preference trial, patients are asked if they have a preference for one specific treatment (PAT or CBT). Treatments are outlined to them in terms of a general description (see box for the instructions). If they articulate a specific preference, they are assigned accordingly (preference arm). If they articulate no specific preference, they are randomized (randomization arm).

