## Discussion

This trial has the major goals: (1) to determine the effectiveness of the two long-term treatments (PAT, CBT) reimbursed in the German healthcare system for chronic depression, and (2) to compare the effects of treatment preference against randomization. It combines the virtues of a randomized controlled (efficacy) trial and a naturalistic approach.

As recent meta-analyses have shown, the treatment of depression by short-term treatments has been plagued by high relapse rates and a lack of lasting effectiveness. Long-term PAT and CBT, however, are not easy to compare, as they differ in frequency (one to three sessions per week), total number of sessions, and duration of treatment (one to three years). We therefore tried to reach comparable doses in the first year of treatment. Initially, psychoanalysts often work with low frequency (≤2 sessions per week) with depressed patients; thus there could be 45 sessions of CBT and up to 80 sessions of PAT in the first year. As our primary outcome is measured at one year (t4), doses of treatment can be compared. When psychoanalytic treatment is continued after one year, dose can be adjusted according to patient need and treatment process. As CBT entails relapse prevention, there will also be an extended treatment duration. In any case, number and timing of sessions will be documented. In this trial, a high quality is assured by an independent assessment.

While patient preferences form one of the three key components of evidence-based medicine, studies on the impact of patient preference on outcome have been scarce. Our design enables us to determine the impact of patient preference on outcome, and we expect a lower attrition rate and a higher effectiveness for preferred vs. randomized assignment.

As this trial has been funded substantially by the German Society for Psychoanalysis, Psychotherapy, Psychosomatics, and Depth Psychology (DGPT), a great effort was made to counteract allegiance effects. The study also is financially supported by the independent, medically oriented Heidehof Foundation (part of the well known Robert Bosch Foundation, Stuttgart). One of the principal investigators (MH) is a renowned cognitive behavior therapist. Data collection, monitoring, and analysis are performed by an independent statistician (BR).

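### The preference-versus-randomised difference can be estimated but not attributed to honouring a preference, and the predicted drop-out difference is planned only as description

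*Protocol article*

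**What the plan says.** All references are to the protocol article.

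- **Hypotheses, B.** The prediction is directional and covers both symptoms and attrition: "Preferred therapies are expected to lead to stronger effects and less study drop-outs than randomized therapies". A further prediction concerns the interaction with treatment: "we expect larger effect differences between PAT preference and PAT randomization compared with CBT".
- **Randomization.** For patients with a preference: "If they articulate a specific preference, they are assigned accordingly (preference arm". For the others: "If they articulate no specific preference, they are randomized (randomization arm". The Design section repeats this for the randomised half: "About 180 patients will come without preference and accept to be randomized to either PAT or CBT".
- **Statistical analysis.** Treatment and assignment are both factors in a repeated-measures model, and the dependence of the CBT–PAT difference on assignment is tested. Intake symptoms are the one covariate named. Cox regression and log-rank tests are given for dichotomous response scores.
- **Secondary analyses.** "Serious adverse events and cases of drop-outs will be analyzed descriptively".
- **Discussion.** The comparison of preference with randomisation is the second of two major goals, and the text says: "Our design enables us to determine the impact of patient preference on outcome". It also expects lower attrition in preferred treatment.
- **Patient preferences (background).** The cited meta-analysis found that "patients who were matched to their preferred treatment were less likely to drop out (OR = 0.59" and that they improved more (d = 0.31).

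**The concern.** The background evidence concerns people who hold a preference and either do or do not receive what they prefer. This design contains no one who states a preference and is then randomised or given the other treatment. The assignment contrast compares people who arrive with a preference with people who arrive without one. If these groups differ in prognosis beyond their intake symptoms, the model attributes that difference to assignment.

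The interaction has the same weakness. Patients who choose PAT and patients who choose CBT are each self-selected, so a larger preference gap in PAT could reflect who chooses PAT.

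What is at stake is the reading of a stated major goal: a selection difference could be presented as an effect of honouring preference. The randomised comparison of PAT with CBT is not affected.

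The drop-out part is a separate mismatch. A directional prediction is made in one section, and the section on analysis provides only description.

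**Working it through.** **1. Which comparisons the design contains.** Cross type of patient with mode of assignment, using the Design and Randomization sections:

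| | Treatment by preference | Treatment by randomisation |
|---|---|---|
| States a specific preference | observed | empty |
| States no specific preference | empty | observed |

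Only the diagonal is filled. Write Y(pref) and Y(rand) for the outcome under each mode, and P = 1 or 0 for having or not having a stated preference. The planned contrast is

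E[Y(pref) | P=1] − E[Y(rand) | P=0]
= {E[Y(pref) | P=1] − E[Y(rand) | P=1]} + {E[Y(rand) | P=1] − E[Y(rand) | P=0]}.

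The first bracket is the effect of honouring a preference. The second is the prognostic difference between the two kinds of patient. Both contain E[Y(rand) | P=1], which belongs to an empty cell, so the data cannot separate them. A larger sample does not change this. Adjustment shrinks the second bracket only as far as the adjusted measures explain it, and the article names intake symptoms alone.

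**2. The interaction.** It is (PAT by preference − PAT randomised) − (CBT by preference − CBT randomised). Each difference carries its own selection term, one for patients who choose PAT and one for patients who choose CBT. These cancel only if the two selection terms are equal.

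**3. Drop-out: is an analysis planned elsewhere?** Hypotheses (B) and the Discussion predict fewer drop-outs. Secondary analyses restricts drop-outs to description. The survival methods under Statistical analysis are tied to response scores. No section shown gives an inferential analysis of drop-out.

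**4. What a formal drop-out test could deliver.** The article states no figure for this, so there is none to reproduce.

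Inputs:
- Odds ratio 0.59, the background value under Patient preferences.
- Randomised-arm drop-out p₁ of 10, 20, 30 or 40%. This is an **assumption**; the article gives no rate.
- Group sizes of 120 versus 120 (Abstract: 240 in total, 60 per arm) and 180 versus 180 (Design: about 360 in total).
- Two-sided α = 0.05.

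Formulas:
- o = 0.59 × p₁/(1−p₁); p₂ = o/(1+o)
- p̄ = (p₁+p₂)/2; SE₀ = √[2p̄(1−p̄)/n]; SE₁ = √{[p₁(1−p₁)+p₂(1−p₂)]/n}
- power = Φ[(p₁−p₂ − 1.96·SE₀)/SE₁]

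Worked case, p₁ = 0.30 and n = 120 per group:
- o = 0.59 × 0.30/0.70 = 0.253, so p₂ = 0.253/1.253 = 0.202
- p₁ − p₂ = 0.098; SE₀ = 0.0560; SE₁ = 0.0556
- power = Φ[(0.098 − 0.110)/0.0556] = Φ(−0.21) ≈ 0.42

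| Assumed p₁ | p₂ | Power, 120 vs 120 | Power, 180 vs 180 | n per group for 80% power |
|---|---|---|---|---|
| 10% | 6.2% | 0.19 | 0.27 | 786 |
| 20% | 12.9% | 0.32 | 0.45 | 421 |
| 30% | 20.2% | 0.42 | 0.58 | 305 |
| 40% | 28.2% | 0.49 | 0.66 | 254 |

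Across this range a test would miss an odds ratio of 0.59 in about a third of trials at best. An interval estimate is the useful output.

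**The case against.** The strongest defence is that B is headed as a comparison of preferred with randomised therapies, and that the article plans exactly that comparison through the assignment factor and its interaction. It openly calls the preference route a naturalistic selection, and it gives a sound external-validity reason for including people who refuse randomisation. This stands. A reader might infer that B has no analysis or cannot be answered at all; the Statistical analysis section shows otherwise. What fails is only the step from an arm difference to the impact of preference.

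Three further readings go too far:

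- **That randomised patients have no preference whatever.** The Abstract speaks of lacking a clear preference and the Randomization section of lacking a specific one. Weak leanings are compatible with both.
- **That d = 0.31 is the effect this trial expects, so a modest prognostic gap would reproduce it.** The figure is background from a meta-analysis. The article sets no effect size for B and gives no information on any prognostic gap, so the size of the bias cannot be stated.
- **That selection will necessarily be reported as a preference effect.** The full analysis plan is not shown and may specify more adjustment. Even so, adjustment would leave the empty cells empty, and the Discussion's claim is made without qualification.

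On drop-out, a descriptive comparison would still show rates by arm, and a test would have low power. Both points are correct. They argue for an estimate with an interval, or for a descriptive label, but they do not remove the mismatch between sections.

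**Conclusion.** The point holds in a limited form. The symptom part of B can be estimated as a difference between arms. That difference cannot be attributed to receiving a preferred treatment, because type of patient and mode of assignment are fully confounded and intake symptoms are the only stated covariate. The Discussion's statement about determining the impact of preference is not supported by the design. This follows from the allocation rules alone and needs no numerical assumption. The direction and size of any bias are unknown.

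Separately, the prediction of fewer drop-outs is matched only by a descriptive analysis. If it were tested at an odds ratio of 0.59, power would be about 0.19–0.49 (120 versus 120) or 0.27–0.66 (180 versus 180). These ranges rest on the assumed 10–40% drop-out, the background odds ratio and two-sided α = 0.05.

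The matter should be corrected because it concerns one of the two major goals.

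**What to change.** 1. **Contrast and wording.** Label the preference-versus-randomised contrast, and its interaction with treatment, as non-randomised comparisons. In addition to intake symptoms, adjust both for prognostic measures that Table 2 already schedules at t0, for example SCL-90R, CTQ, DEQ, IIP, OPD-2 and SOFAS. In the Discussion, speak of estimating an association instead of determining an impact, and note that residual confounding remains. Motivation, education and earlier therapy are plausible confounders but are not among the t0 measures in Table 2, so these adjustments may not capture them.
2. **Drop-out.** Reconcile Hypotheses (B) with Secondary analyses. Either prespecify an odds or hazard ratio for drop-out by assignment, with a confidence interval, over a common 12-month period (the two treatments differ in length), or label the prediction as descriptive.
3. **Optional.** Recruitment is ongoing, so patients still to be enrolled could give a short rating at t0 of their leaning toward each treatment. Within the randomised arm, those allocated with and against their leaning could then be compared as an exploratory analysis. It would use at most the randomised half, leanings there may be weak, and ratings would be missing for patients already enrolled.

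Items 1 and 2 need only changes to text and analysis specification, with no new data. The real cost is a weaker claim for the second major goal.
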